**Methods:**

A prospective, randomized-controlled trial design is applied. Patients with unilateral first-time patella dislocation will be considered for participation. Study participants will be randomized to either conservative treatment or to a tailored patella stabilizing treatment. In the conservative group, patients will use a knee brace and will be prescribed outpatient physical therapy. The surgical treatment will be performed in a tailored manner, addressing the pathologic anatomy that predisposes to patella dislocation.

The Banff Patellofemoral Instability-Instrument 2.0, recurrence rate, apprehension test, joint degeneration, and the Patella Instability Severity Score will serve as outcome parameters. The main analysis will focus on the difference in change of the scores between the two groups within a 2-year follow-up.

Statistical analysis will use linear mixed models. Power analysis was done for the comparison of the two study arms at 2-year follow-up with regard to the BPII Score. A sample size of N = 64 per study arm (128 overall) provides 80% power (alpha = 0.05, two-tailed) to detect a difference of 0.5 standard deviations in a t-test for independent samples.

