### Other outcome parameters

Recurrence rate is assessed as second major outcome parameter (hypothesis 2). To keep proper medical records on recurrent patella dislocations, the patients are interviewed by telephone on a monthly basis (in addition to the abovementioned visits at the hospital).

The apprehension test is assessed by an experienced observer during the abovementioned routine clinical visits (grade 0, no evasion; grade 1, slight evasion/avoidance; grade 2, gross evasion/avoidance; grade 3, patient too anxious to allow the test).

Joint degeneration is assessed preoperatively and every three years postoperatively by means of MRI (PD-FSE with fat-sat high-resolution in all three planes/T1-TSE, sagittal/T2 weighted, isotrope 3D sequence sagittal reformatted in all three planes). The semi-quantitative MRI Osteoarthritis Knee Score (MOAKS scoring) is applied to rate the degenerative changes determined by MRI [56]. The MOAKS scoring is determined by always the same experienced musculoskeletal radiologist. Additionally, TT-TG distance is measured on postoperative MRI.

In addition, the Patella Instability Severity Score is assessed for exploratory reasons [57].

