### Statistics

Patient characteristics will be presented as means, standard deviations, and percentages. The main analysis will use linear mixed models that allow data modeling with a varying number of assessments per patient and time-varying covariates. Such a model will be used to compare the differences in changes over time between the two study groups. The following terms will be included in the model: a random baseline, a first-order autocorrelation covariance matrix, a fixed-effect patient group, a fixed effect time point, and the group-by-time interaction (reflecting the intervention effect). The BPII 2.0 will serve as the primary outcome parameters. The main analysis is “intention to treat” and will focus on the group difference in the change of BPII 2.0 scores between pre-op and 2-year follow-up. The abovementioned secondary outcome parameters will be analyzed with the same model.

Power/sample size analysis was done for the comparison of the two study arms at a 2-year follow-up with regard to the BPII Score. As there are no specific minimal important difference (MID) for the BPII available from the literature, we defined the MID to be 0.5 standard deviations following general recommendations from the literature [58]. A sample size of N = 64 per study arm (128 overall) provides 80% power (alpha = 0.05, two-tailed) to detect a difference of 0.5 standard deviations in a t-test for independent samples. To account for 20% attrition during the study period (“dropouts”), we plan to recruit 80 patients per study group (160 overall) at baseline.

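### The single linear mixed model assigned to the secondary outcomes does not suit recurrence (hypothesis 2), which is zero for every patient at baseline, so its standard errors would be wrong

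*Protocol article*

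**What the plan says.** The Statistics section describes one model, with these terms: "a random baseline, a first-order autocorrelation covariance matrix, a fixed-effect patient group, a fixed effect time point, and the group-by-time interaction". The main analysis "will focus on the group difference in the change of BPII 2.0 scores between pre-op and 2-year follow-up". On rank, it states "The BPII 2.0 will serve as the primary outcome parameters", and then extends the method: "The abovementioned secondary outcome parameters will be analyzed with the same model". The abstract is equally general: "Statistical analysis will use linear mixed models".

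Under Other outcome parameters the article says "Recurrence rate is assessed as second major outcome parameter (hypothesis 2". It adds that, to record re-dislocations, "the patients are interviewed by telephone on a monthly basis". The same section defines the apprehension test as four ordered grades, the highest being "grade 3, patient too anxious to allow the test".

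Study design and participants admits only first-time dislocation and excludes recurrent dislocation. No binary, survival, count or ordinal method is named anywhere in the article.

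**The concern.** Recurrence is an event, not a score. Coded as has or has not re-dislocated by each visit, it equals 0 for every patient at baseline. A random baseline therefore has nothing to describe, and the change from baseline is simply the 2-year value. The variance starts at zero and then moves with cumulative incidence, whereas a random intercept plus AR(1) residual imposes the same variance at every visit. Standard errors, p values and confidence intervals for hypothesis 2 would come from a covariance structure that cannot hold.

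The model also uses only the status at hospital visits. The monthly calls show roughly when a re-dislocation happened, and how long a patient lost to follow-up was known to be free of one. With 20% attrition planned for, that information matters.

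This differs from a detail left to an analysis plan that is not shown, because the article positively assigns a method.

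**Working it through.** **1. The plan's own figure.** The sample size is for the BPII: 0.5 SD, two-sided 5%, 80% power. The normal approximation gives 2 × (1.960 + 0.842)² / 0.5² = 62.8, so 63 per arm. The exact t calculation gives 63.77, so 64, with power 0.801. Allowing for 20% attrition, 64 / 0.8 = 80 per arm. The stated 64 and 80 reproduce, and nothing below affects them.

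**2. Inputs for recurrence.** From the article: visits at 0, 6, 12 and 24 months, baseline value 0, and the model terms. Assumed, because the article gives none: recurrence rates, coding as a cumulative 0/1 state, AR(1) over visit number, model-based standard errors, and no treatment effect.

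**3. True covariance.** With cumulative risk p at each visit, Var(t) = p_t(1 − p_t) and Cov(s,t) = p_s(1 − p_t) for s < t. For assumed risks of 0/8/15/25% the variances are 0, 0.0736, 0.1275 and 0.1875. The 24-month-minus-baseline contrast has true variance 0.25 × 0.75 = 0.1875 per patient.

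**4. Best-fitting model covariance.** Let V = random intercept + AR(1) with common variance, chosen to minimise log|V| + tr(V⁻¹S), where S is the true covariance. For these risks the intercept variance goes to zero, the residual variance is 0.0964 and the correlation is 0.607. The model's contrast variance is 2 × 0.0964 × (1 − 0.607³) = 0.150.

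**5. Consequence.** SE ratio = √(0.150 / 0.1875) = 0.894, so the standard error is understated by about 11%. True type I error = 2 × [1 − Φ(1.96 × 0.894)] = 8.0%.

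**6. Range over assumed rates, same method.**

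| Cumulative risk at 0/6/12/24 months | SE ratio | Type I error |
|---|---|---|
| 0/4/7/12% | 0.860 | 9.2% |
| 0/8/15/25% | 0.894 | 8.0% |
| 0/10/18/30% | 0.909 | 7.5% |
| 0/12/22/40% | 0.938 | 6.6% |
| 0/16/29/50% | 0.988 | 5.3% |
| 0/20/35/60% | 1.051 | 3.9% |

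With AR(1) over calendar time instead of visit number, the 25% row becomes 7.0% and the 12% row 8.3%.

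**7. Check by simulation.** This used 64 per arm, complete data, exponential time to first recurrence, the article's model and 1,500 runs per scenario. The Monte Carlo error near 5% is √(0.05 × 0.95 / 1500) = 0.6 percentage points.

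| 2-year recurrence, both arms | Mixed model, type I error | Chi-square at 2 years, type I error | Mean model SE | Actual SD | 95% CI coverage |
|---|---|---|---|---|---|
| 20% | 9.3% | 5.3% | 0.061 | 0.072 | 91% |
| 30% | 7.8% | 5.1% | 0.073 | 0.080 | 92% |
| 40% | 5.7% | 4.5% | 0.081 | 0.083 | 94% |

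The two methods agree on direction and approximate size.

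**The case against.** **Does the sentence cover recurrence?** The article calls recurrence the second of two major outcomes and never calls it secondary. The abstract describes the main analysis as a comparison of change in scores, and recurrence is not a score. On that narrower reading the method for hypothesis 2 is merely unstated, which an article may leave to a fuller document. The ambiguity is real. Still, only the BPII is named as primary, there is no separate list of secondary outcomes, and no other method is offered. The wider reading is therefore the more natural one, and under either reading the sentence needs a limit.

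**Is the estimate meaningless?** A reader might infer so, but it is not. When everyone starts at 0, the group difference in change to 2 years is the 2-year risk difference, given complete data and 0/1 coding. The fault lies in its standard error and in the unused follow-up information.

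**Are the standard errors always too small?** A reader might infer this too. The table in the working shows otherwise: the error fades near 50% recurrence and reverses at 60%. The article gives no rates that would settle which applies.

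**Does hypothesis 2 need event timing?** Its wording does not ask for it, and a comparison of 2-year proportions would answer it with complete data. The case for a survival method rests on expected attrition. The article also does not say that event dates are recorded, only that patients are called monthly.

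**Apprehension.** The baseline-zero argument does not reach this outcome. Its top grade is a defined category of an ordered scale, not a missing value, and a linear model for a 0–3 grade is a common approximation. An ordinal mixed model would suit it better, but that is a preference.

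**Conclusion.** The point holds in limited form. On its most natural reading, the article assigns recurrence a model whose constant-variance assumption is contradicted by the trial's own eligibility rule, so inference on hypothesis 2 would be wrong. At an assumed 2-year recurrence of 12–30% the nominal 5% test runs at about 7–9%, which makes a difference too easy to declare. At higher assumed rates the error shrinks and then turns conservative. These figures depend on the assumed rates, cumulative 0/1 coding, four visits and model-based standard errors.

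The BPII analysis and its sample size are unaffected. The effect is moderate and falls on a non-primary outcome. It should still be corrected before analysis, because recurrence carries one of the trial's two stated hypotheses and the correction is cheap.

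**What to change.** - In Statistics, limit the shared model to the continuous scores: BPII 2.0, Kujala, SF-12 and Marx.
- State a separate analysis for hypothesis 2: first re-dislocation by 2 years, with Kaplan-Meier 2-year risks by arm, their difference with a 95% CI, and a log-rank test. Censor patients without an event at last contact, including the last telephone call. If only the month of the event is known, use interval-censored versions.
- Make the matching change to the general statement on methods in the abstract.
- Optionally, name an ordinal mixed model for the apprehension grade, which keeps the repeated assessments.

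The cost is a few lines of wording, plus making sure the monthly call form records the month of each re-dislocation. No extra patients, visits or measurements are needed.

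### The 80% power is calculated for a t-test of 2-year BPII scores, but the named main analysis is the difference in change from baseline, for which that power is not established

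*Protocol article*

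**What the plan says.** All quotes are from the protocol article.

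- **Sample size (Statistics).** The calculation concerns the comparison of the arms' BPII scores at 2 years: 64 patients per arm "provides 80% power (alpha = 0.05, two-tailed) to detect a difference of 0.5 standard deviations in a t-test for independent samples". The target difference is standardised: "we defined the MID to be 0.5 standard deviations following general recommendations from the literature". Allowing for 20% attrition, 80 per arm are to be recruited.
- **Main analysis (Statistics).** The analysis is by intention to treat and "will focus on the group difference in the change of BPII 2.0 scores between pre-op and 2-year follow-up". The abstract agrees: "The main analysis will focus on the difference in change of the scores between the two groups within a 2-year follow-up".
- **Model (Statistics).** A linear mixed model has a random baseline term, a first-order autocorrelation structure, and fixed effects for group, time point and group-by-time. The interaction is named as the intervention effect. Pre-op is one of the modelled time points, and baseline BPII is not listed as a covariate.
- **Hypothesis 1 (Hypotheses).** The arms are expected to differ in BPII 2.0 after two years.

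The article gives no SD in BPII points, no SD of change and no baseline to 2-year correlation.

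**The concern.** The hypothesis and sample size refer to the 2-year score, while the analysis refers to change since baseline. Under randomisation both target the same treatment effect, but their precision differs. A change score carries the variability of the baseline as well as that of the endpoint. Unless the two are correlated strongly enough, subtracting the baseline adds more noise than it removes.

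The mixed model does not avoid this. With time as a category, a free group effect and complete data, the 2-year interaction contrast equals the difference in mean change. Randomisation makes a free baseline group difference unnecessary, and estimating it costs precision.

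Baseline is taken around an acute first dislocation and the endpoint is two years later, after treatment. A modest correlation is therefore conceivable, but that is a judgement and not a figure from the article. What is at stake is whether the 80% on which recruitment of 160 patients rests applies to the test that will be reported.

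**Working it through.** **Inputs from the article (Statistics):** two-sided alpha 0.05; 64 evaluable per arm; 80 recruited per arm with 20% lost; difference 0.5 SD of the score. Visits (Patient-reported outcome): pre-op, 6, 12 and 24 months.

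**Assumptions, not in the article:** rho, shown over a range; equal SDs at baseline and 2 years, relaxed in step 4.

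**1. The stated figure.** For a t-test with n = 64 per arm, the noncentrality is 0.5 × √(64/2) = 2.83 on 126 degrees of freedom. Power is 80.1%; with 63 per arm it is 79.5%. So 64 is right, and 64/0.8 = 80 is right.

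**2. Difference in change, completers only.** The variance of change per patient is 2(1 − rho)SD², so the standardised effect is 0.5/√(2(1 − rho)). At rho = 0.3, √1.4 = 1.183 and 0.5/1.183 = 0.423, which gives 66% power.

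**3. Baseline-adjusted 2-year score, completers only.** The residual variance is (1 − rho²)SD², so the standardised effect is 0.5/√(1 − rho²).

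| rho | Power, change | n per arm for 80%, change | Power, baseline-adjusted |
|---|---|---|---|
| 0 | 51% | 127 | 80% |
| 0.2 | 60% | 102 | 82% |
| 0.3 | 66% | 89 | 84% |
| 0.4 | 73% | 77 | 86% |
| 0.5 | 80% | 64 | 90% |
| 0.6 | 88% | 52 | 94% |

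**4. Unequal SDs.** The variance of change is SD_baseline² + SD_2yr² − 2·rho·SD_baseline·SD_2yr. Setting this equal to SD_2yr² gives the completer threshold rho = SD_baseline/(2 × SD_2yr). It is 0.30 at an SD ratio of 0.6, 0.40 at 0.8, 0.50 at 1 and 0.625 at 1.25.

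The variance of change minus the adjusted variance, (1 − rho²)SD_2yr², equals (SD_baseline − rho·SD_2yr)². This is never negative, so adjustment has no larger variance than change whatever the two SDs are.

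**5. Partial data from dropouts.** The planned model also uses incomplete patients. The variance of the 2-year interaction contrast was computed by generalised least squares under a random intercept plus AR(1), with 80 per arm and 20% lost, using the normal approximation.

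- Example: intercept share 0.3 and autocorrelation 0.3 per six months, so rho = 0.306. Completers alone give 67.0%. With partial data, power is 70.1% if all losses follow baseline, 70.7% if all follow 12 months, and 70.4% if they are spread.
- Across the structures tried, power at rho 0.3 is about 70–71%, and 80% is reached at rho of about 0.44–0.47.

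**The case against.** - **No shortfall is demonstrated.** A reader might infer that the trial is underpowered. The article does not support this, because it gives no correlation. Above rho 0.5 with equal SDs the change analysis exceeds 80% even among completers. This objection stands.
- **The 0.5 threshold is not exact.** A reader might also infer that power is below 80% whenever rho is below 0.5. That holds only for 64 completers per arm with equal SDs. The planned model uses partial data, which lowers the threshold to about 0.44–0.47, and unequal SDs move it either way. This stands too.
- **The 0.5 SD might mean the SD of change.** Power would then be 80% by definition. The Statistics section, however, ties the calculation to the comparison of BPII scores at 2 years, so this is not its natural reading.
- **The planned estimate is valid.** With a baseline recorded before allocation, the difference in change is unbiased and type I error is unaffected. This is correct, and it makes the point one of efficiency and justification.
- **The remedy has limits.** Adjustment costs one degree of freedom and a little for chance baseline imbalance. At rho 0, power is then about 79.8% rather than 80.1%, so 80% is not a strict lower bound. A model with a common baseline mean also needs BPII recorded before allocation. The sections on participants, randomisation and patient-reported outcome say only that scores are taken preoperatively. Both limits stand, and neither removes the case for adjustment.

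**Conclusion.** The mismatch is certain: the stated 80% belongs to a t-test of 2-year scores and not to the group-by-time analysis named as primary. The sample-size arithmetic itself is correct.

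The size of the consequence is conditional. With equal SDs, power for a true 0.5 SD difference could be as low as 51% among completers at rho 0. It is 66% at rho 0.3, or about 70–71% with partial data from dropouts, and it is above 80% at higher correlations. Because the article states neither rho nor the SDs, the supportable conclusion is that power is not established for the named analysis. It does not follow that the trial lacks it.

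The change estimate is unbiased but less efficient than a baseline-adjusted one. Severity: should be fixed, before the comparison is run.

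**What to change.** Define the primary comparison as the group difference in mean BPII 2.0 at 2 years, adjusted for baseline BPII. Either form of the mixed model will do:

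- baseline BPII as a covariate, with the post-baseline visits as outcomes; or
- all visits as outcomes with a common baseline mean in both arms (time plus group-by-post-baseline time, no group term at baseline), provided BPII is recorded before allocation.

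State when baseline BPII is completed relative to randomisation. Keep 64 evaluable and 80 recruited per arm. State that power for a 0.5 SD difference is about 80% at rho 0 and higher otherwise (about 84% at 0.3, 90% at 0.5).

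If the difference in change is kept as primary, state the assumed rho and both SDs and size the trial on the SD of change. That could require more patients; for example, 89 evaluable per arm (112 recruited) at rho 0.3 on the completer calculation.

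The recommended change affects analysis wording only and needs no extra patients, visits or data. It also brings the main analysis into line with hypothesis 1 and the sample size.

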## Data Availability

The datasets used and/or analyzed during the current study are available from the corresponding author on reasonable request.

## Abbreviations

3D: Three-dimensional
AGA: Gesellschaft für Arthroskopie und Gelenkchirurgie
BPII: Banff Patellofemoral Instability-Instrument
CT: Computer tomography
EC: Ethics committee
ICF: Informed consent form
LPD: Lateral patella dislocation
MID: Minimal important difference
MOAK scoring: MRI Osteoarthritis Knee Score
MPFL: Medial patellofemoral ligament
MRI: Magnetic resonance imaging
N: Sample size
PD-FSE: Proton density-fast spin echo
PF: Patellofemoral
PROM: Patient-reported Outcome Measures
SF-12v2: Short-Form 12 version 2
TSE: Turbo spin echo
TTT: Transfer of the tibial tuberosity
TT-TG distance: Tuberositas-tibiae-trochlea-groove distance
